### Study visits

All participants undergo a baseline study visit and the 24-week behavioral weight loss program. They complete remote questionnaires at weeks 8, 16 and 24 of the program, then, during follow up at 9-, 12-, 15- and 18-months after the start of the behavioral weight loss program [Fig 5]. Baseline visits occur within approximately 30 days after the eligibility visit and procedures are completed on two separate study days. Participants are eligible to be invited to complete additional in-person visits if they meet the study-defined weight change criteria described above. In-person visit types triggered in real time based on participants’ individual weight loss trajectories include: active weight loss visits, weight loss plateau visits (occurs over 2 days), and supplemental weight loss plateau visits if the initial plateau is not confirmed by interim threshold regression modeling (as described above in *Remote weighing and real-time classification of phase of weight loss*). By nature of the study criteria, a plateau visit would occur at least 21 days after an active weight loss visit. Plateau and supplemental plateau visits follow the same two-day protocol as baseline visits, whereas active weight loss visits involve an abbreviated single-day protocol [Fig 6]. For all visit days, participants arrive following an overnight fast and having refrained from exercise within the past 24 hours.

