**Fig 6 pone.0354678.g006:**
[figure not shown]
ADAPT In-Person Visit Day paradigms. Baseline and plateau visits occur over two days, active weight loss visits occur over a single day following the ‘Day 2’ paradigm. For all visit days, participants are asked to fast overnight and refrain from exercise for the previous 24 hours. The Day 1 paradigm begins with an IV placement, fasting blood draw, then anthropometric measures, vital sign measurements, and a dual x-ray absorptiometry (DXA) scan. Behavioral questionnaires, including cognitive assessments (i.e., General Cognitive Index and Go/No-Go) are completed. A fasted MRI (#1), including fMRI visual food cue task and structural MRI of the hypothalamus, is completed, then participants are presented with a standardized meal of macaroni and cheese and asked to consume it within 10 minutes. A fed MRI (#2) is completed 30 minutes after meal initiation and includes fMRI of visual food cues and resting state. Serial blood draws occur at time 0 (just prior to the standardized meal), then 30- and 60-minutes after the meal. Serial subjective appetite ratings by visual analog scale are administered throughout day 1 (i.e., upon arrival, after the DXA, prior to MRI #1, before and after the standardized meal and after MRI #2). Day 1 is completed at the University of Washington. The Day 2 paradigm begins with indirect calorimetry procedures, followed by a fasting blood draw and muscle and adipose tissue biopsies. Day 2 is completed at the Fred Hutchinson Cancer Center.

As part of the Day 1 visit protocol, participants complete questionnaires and undergo weight, waist and neck circumference, vital sign measurements, and DXA. Serial blood draws occur throughout the visit day (AM fasting, pre-meal (also in a fasted state), 30- and 60-min post standardized meal). Cognitive assessments are completed on a desktop computer. Next, participants complete a pre-meal MRI session, consume a standardized meal, then a post-meal MRI session. Day 1 procedures are completed at the University of Washington. For the Day 2 visit protocol, completed at the Fred Hutch Cancer Center, indirect calorimetry procedures are completed, followed by a fasting blood draw and muscle and tissue biopsies. All procedure details are below.

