#### Aim 3.

The primary outcomes of interest being explored in Aim 3 are entry into a weight loss plateau (Yes/No) and time from baseline (beginning of behavioral weight loss program) to plateau entry (continuous). Entry into a weight loss plateau will be defined as the 1) day at which a subject met weight loss plateau criteria during real-time monitoring or 2) first day of a weight loss plateau identified via threshold regression modeling at study completion. *A priori* predictors of interest for Aim 3 are based on available literature and our own findings and include the slope of the first active weight loss period [64]; trends over time in craving for carbohydrates/starches, dietary restraint, and disinhibition [65]; changes in T-cell and muscle maximal respiratory capacity; fasting ghrelin [66]; and baseline central satiety response, mediobasal hypothalamic T2 relaxation time [67], leptin [28] concentrations, and HOMA-IR [68]. Other predictors (i.e., inhibitory control) may be tested based on the findings of Aims 1 and 2; remaining predictors will be considered exploratory. Analyses will include only participants who achieved active weight loss. Fully adjusted models will include baseline or change in % body fat. Sensitivity analyses will be completed to evaluate whether excluding participants not achieving adherence will have the same or better predictive capabilities. A sample size of N = 40 participants who achieve active weight loss provides 91% power to detect effect sizes of R^2^ ≥ 0.36 at P < 0.05 for continuous outcomes.

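### Aim 3 allows adjustment for change in % body fat, which by the visit text can be measured only after plateau entry, the outcome being predicted

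*Protocol article*

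**What the plan says.** On outcomes, the Aim 3 section of the statistical analysis plan says: "The primary outcomes of interest being explored in Aim 3 are entry into a weight loss plateau (Yes/No) and time from baseline", running to plateau entry. On the analysis set: "Analyses will include only participants who achieved active weight loss". This includes people who lose weight and never plateau. On adjustment: "Fully adjusted models will include baseline or change in % body fat".

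The timing of % body fat follows from the visit descriptions. The Fig 6 caption puts "anthropometric measures, vital sign measurements, and a dual x-ray absorptiometry (DXA) scan" in the Day 1 paradigm, and the text below it repeats that on Day 1 "participants complete questionnaires and undergo weight, waist and neck circumference, vital sign measurements, and DXA". Baseline and plateau visits have both days. For the intermediate visit the caption says "active weight loss visits occur over a single day following the" Day 2 paradigm, and Day 2 lists calorimetry, a fasting blood draw and biopsies. The Study visits section agrees: "whereas active weight loss visits involve an abbreviated single-day protocol". Under the section on remote weighing, a plateau visit is booked for the two weeks after the real-time criteria are met.

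The Aim 3 predictors include "trends over time in craving for carbohydrates/starches, dietary restraint, and disinhibition" and changes in respiratory capacity, with no end of window given for either.

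**The concern.** A covariate in a model of whether or when an event occurs should be known before the event and for those who never have it. Change in % body fat appears to fail on both counts.

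In the Yes/No model, having a value at all nearly identifies the outcome. In the time model, someone who loses fat for longer has lost more by the plateau visit, so the covariate carries the outcome inside it. Predictors that merely track the speed of fat loss could then be reported as predictors of early plateau, which is the inference Aim 3 is meant to support.

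**Working it through.** **1. The plan's own figure.** Aim 3 states 91% power for N = 40, R² ≥ 0.36, P < 0.05. The number of predictors is not given. For an overall F test, f² = 0.36/0.64 = 0.5625 and λ = 40 × 0.5625 = 22.5. Power is 94.3% with five predictors, 92.2% with six, 89.8% with seven and 87.3% with eight. So 91% is plausible for six or seven predictors but cannot be confirmed. Nothing below depends on it.

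**2. Who has a change value.**

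| Visit | Day 1 (with DXA) | Day 2 |
|---|---|---|
| Baseline | yes | yes |
| Active weight loss | no | yes |
| Plateau, supplemental plateau | yes | yes |

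A participant who never triggers a plateau visit has only the baseline scan, so change is undefined. One group of non-events can have a second scan: those with a real-time plateau visit that the final threshold model does not confirm, if entry is defined by that model.

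**3. When it is measured.** The plateau scan follows the day on which the real-time criteria are met. If the threshold model confirms the plateau at that visit, the scan also follows the first day of the modelled plateau. Either way it comes after the event.

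**4. How much of the outcome it contains.** Write fat change at plateau as C = r·T + e, where T is weeks to plateau and r is the weekly rate of fat loss. The inputs are assumptions, not trial figures: T has mean 26 and SD 8, r has mean 0.15 and SD 0.05 points per week, independent of T, and e has SD 0.5.

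- Cov(C, T) = 0.15 × 64 = 9.6
- Var(C) = 0.15² × 64 + 26² × 0.05² + 0.05² × 64 + 0.5² = 1.44 + 1.69 + 0.16 + 0.25 = 3.54
- Squared correlation of C with T = 9.6² / (64 × 3.54) = 92.16 / 226.56 ≈ 0.41

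The covariate alone would explain about 41% of the variance in time to plateau, by construction.

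**5. What that does to a null predictor.** A simulation used N = 40, the same inputs with T truncated to 6–60 weeks, and 6,000 replicates per setting. The predictor has no effect on T but has correlation ρ with r. Entries are the rejection rate at a nominal 5%, with mean model R² in brackets.

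| ρ | Unadjusted | Fat change over a fixed 4-week early window | Fat change at plateau |
|---|---|---|---|
| 0 | 5.0% (0.03) | 4.9% (0.05) | 5.2% (0.42) |
| 0.3 | 5.0% (0.03) | 5.1% (0.05) | 19.5% (0.44) |
| 0.5 | 4.7% (0.03) | 5.0% (0.05) | 49.1% (0.48) |
| 0.7 | 4.7% (0.03) | 4.7% (0.05) | 85.4% (0.54) |

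The mechanism is simple: at a given total fat loss, a faster rate means a shorter time. Holding C fixed therefore ties anything related to r to T. Mean R² passes the 0.36 used for planning even when the predictor does nothing.

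**6. Predictor windows (secondary).** The serial questionnaires fall at weeks 8, 16 and 24 and months 9, 12, 15 and 18, regardless of plateau entry. For an illustrative plateau at week 20, two precede it and five follow. Pre-plateau data do exist: Table 1 schedules the craving and eating-behaviour instruments at baseline and the active weight loss visit, and biopsies and fasting blood are also taken at that visit.

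**The case against.** The strongest objection is that the Day 2 list is not a full account of the active weight loss visit. The behavioural tasks and several questionnaires are also done there, although Fig 6 shows them under Day 1. The Clinical measurements paragraph opens by covering every visit type and mentions DXA without restriction. The schedule in Fig 2, which could settle the matter, is not shown. This lowers certainty. However, the passages that assign procedures to visit days place DXA on Day 1 only, and if DXA were done at active visits the text would still have to confine change to the baseline-to-active interval.

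A second objection is that the wording offers baseline or change, and baseline is sound. That is correct: the plan permits the faulty model but does not commit to it.

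Third, a reader might infer that every non-event is lost and the Yes/No model cannot be fitted at all. The documents do not support that, because unconfirmed plateau visits supply some scans among non-events.

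Fourth, a reader might infer that the Aim 3 models as a whole condition on the outcome, with predictors running past the plateau. The documents do not say so. Windows are left open and may be set in a fuller plan, several predictors are explicitly baseline measures, the slope of the first active phase is a rate before entry, and respirometry change can be taken at the active visit. What stands is a request to state the cut-off.

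**Conclusion.** The concern holds for the change option in the adjustment sentence. On the specific visit text, that option removes nearly all non-plateau participants from the Yes/No model and puts a post-event, outcome-dependent covariate into the time model. The rejection rates of about 20% to 85% show what could happen under assumed inputs; they do not estimate this trial's error rate. They require a predictor related to the rate of fat loss. With no such relation the test keeps its 5% level, although R² is still inflated.

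The conclusion rests on DXA being absent from active weight loss visits. The predictor windows are a secondary clarification. Because Aim 3 is exploratory and the Aim 1 and Aim 2 comparisons are untouched, this is a moderate point and not a condition for proceeding.

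**What to change.** In the Aim 3 adjustment sentence, delete *or change in*, so that the fully adjusted models use baseline % body fat. This matches Aims 1 and 2, where % body fat appears only as a baseline covariate.

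If a measure of progress is wanted, use % weight change from the daily scale over a fixed window that ends before plateau entry. Under the real-time definition, the first four weeks of the programme qualify for everyone, because nobody can meet plateau criteria without first meeting active-loss criteria. The Introduction notes that such early loss partly reflects body water, so the choice of window should be justified.

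Add one sentence limiting the questionnaire trends and respiratory-capacity changes to data recorded before plateau entry, for example from baseline to the active weight loss visit. The stated outcome, time from baseline, need not change.

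The cost is a change of wording and slightly less data per predictor. No new measurements are needed.

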## Discussion

The ADAPT study is poised to make novel contributions to scientific understanding of volitional weight loss. It implements unique design elements that assess tissue-level bioenergetics as well as neurophysiologic and behavioral outcomes. These elements address gaps in the literature and could provide insights into mechanisms resulting in an involuntary weight loss plateau. Consequently, findings could be informative in several respects. They could suggest modifications to lifestyle change recommendations to extend weight loss, uncover potential molecular targets involved in modulating energy consumption and efficiency during weight loss, or identify neural pathways that underlie the appetitive responses that can resist weight loss or produce symptoms of hunger, loss of satiety or pervasive thoughts of food. Any of these discoveries could be further investigated to determine their role in the occurrence of weight loss plateaus during other modes of treatment, including metabolic surgery or pharmacologic treatments. Additionally, the findings could be applied to better understand physiological drivers of weight maintenance and to identify ways of supporting long-term weight maintenance. In sum, the ADAPT study shows potential to advance therapeutic options for prolonging the weight loss phase, attaining a greater degree of weight loss when it is required for health benefits, and contributing to knowledge of the aspects of weight loss that improve health outcomes for patients.
